### Study timeline and visits

Illustrated in
Figure 1 (Phase I) and
Figure 2 (Phase II), eligible subjects will be identified using pre-screening and screening procedures, as described above. Once an eligible subject is identified and wishes to participate, they will complete an enrollment visit for which informed consent (Supplementary File 2, available as
*Extended data*
^21^) is obtained and instructions for stool sample collection are reviewed. The eligible subject is then randomized to a treatment group. The subject returns for a baseline, pre-intervention visit (week 0) for which a stool sample, fasted blood sample and questionnaire assessing signs and symptoms of gastrointestinal health (Gut Irritation Questionnaire) are collected, followed by standard continental breakfast (English muffin or bagel, spreads, coffee, juice and fruit). Oranges (juice, marmalade, or fresh fruit), and teas will not be offered, as those foods decrease the absorption of iron in the body. Immediately following breakfast, subjects will be administered the assigned intervention agent. After 2 hours, a post-prandial, post-dose, blood sample is collected. Instructions for intervention agents are reviewed with the subjects and they are dispended study supplements sufficient for 4 weeks. During the 4-week intervention period, subjects complete weekly Gut Irritation Questionnaires in addition to three 24-hour dietary recalls via telephone. After the 4-week intervention, subjects return for a post-intervention visit which follows the same procedures as the baseline visit.

**Figure 1. f1:**
[figure not shown]
Phase I CONSORT flow chart.

**Figure 2. f2:**
[figure not shown]
Phase II CONSORT flow chart.

## Methods: Assignment of interventions

### Randomization and blinding

The allocation sequence constructed using a block randomization with a block size of four. Random ordering of the allocations within each block was performed using for the study was performed using SFMT (SIMD-oriented Fast Mersenne Twister) algorithm (version 1.5.1) based randomization functions in the “StatsBase” Julia package. No stratification was used in the randomization, and the allocation sequence was implemented using the built-in “randomization” module in REDCap. This module references the provided allocation table and assigns participants based on order of enrollment.

For Phase I, subjects will be randomly assigned to one of the six treatment arms outlined in
Figure 1 at the time they enroll in the study. A randomization scheme for all entering subjects will be generated and stored by the Data Manager. The randomization sequence is known only to the Data Manager, and REDCap user roles were used to prohibit access to the allocation sequence until the participant was randomized to a treatment group. The unblinded key is maintained by the data manager and stored in a locked filing cabinet until the data collection for the study is complete. An active control group, using a corn starch placebo, will be used to provide a control for prospective changes over time and mimic any effects of ingesting a daily capsule in case it may be relevant. We will also provide placebo capsule to all other groups to blind against the FeSO
_4_ plus MNP group. All daily interventions groups will receive three physically similar capsules to ensure blinding of the treatments. The weekly intervention group will receive four physically similar capsules once per week.

For Phase II, subjects will be randomly assigned to one of the three treatment arms outlined in
Figure 2 at the time they enroll in the study. The randomization scheme will be the same as Phase I. We will not employ a control group in Phase II because any prospective changes over time or effects of ingesting a daily capsule will be determined from Phase I. All groups will receive four physically similar capsules to ensure blinding of the treatments.

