***Bias, confounding, effect modulators.*** Due to the completely randomized design, there will be protection of bias in treatment effects from known and unknown confounding variables. We will also compare subject characteristics across treatment groups and adjust for confounding effects for any variables not balanced through randomization. We are unaware of effect modulators of iron supplementation on
*P. falciparum* infectivity and bacterial proliferation. However, outcomes will be evaluated separately at different covariate levels to look for possible modulating effects to be included as interaction terms in our models. Potential effect modulators for fecal calprotectin include age and sex
^35^, and we plan to include them in the models for this outcome.

***Power calculations and sample size.*** The sample size of Phase I and Phase II was determined based on power calculations for each primary outcome as follows:

1) 
Malaria infectivity: The sample size is based on standard deviation estimates from the
*in vitro* assay of malaria infectivity by Clark
*et al.* (2014)
^36^. We pooled the estimated variability of percent increase of
*P. falciparum* growth analyzed in Clark
*et al.* (2014). Using an independent two-sample t-test, an estimated standard deviation 0.202, with a type I error of 0.05, we have at least 90% power to detect a 20% reduction in
*P. falciparum* growth using a minimum of 25 subjects per group. 2) 
Bacterial proliferation potential: Bacterial proliferation potential due to oral iron supplementation was previously studied from a similar
*ex vivo* assay
^23^. Between subject estimates of standard deviation were extracted for doubling time during the exponential phase of growth available from three species,
*S. aureus*,
*E. coli*, and
*S. Typhimurium* as 0.2470, (0.530 and 0.212), and (0.813 and 0.071), respectively, with unequal variance estimates used for
*E. coli* and
*S. Typhimurium* from pre- and post-iron supplementation. Based on two-sample t-tests with type I error at 0.01 (adjusted for planned analysis of five species), and assuming 25 subjects per group, with a minimal detectable difference of 1 hour doubling time, the power is >0.99 for all three species,
*S. aureus*,
*E. coli*, and
*S. Typhimurium*. 3) 
Fecal calprotectin: Estimates of between subject variation are from subjects with various forms of mild gastrointestinal disease

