^30^. Mean fecal calprotectin was reported at 27.6 μg/g in subjects with collagenous colitis, representing mild inflammation, and at 1.9 μg/g in subjects with irritable bowel syndrome, reflecting minimal inflammation. Standard deviation in log concentration of fecal calprotectin used in the sample size calculation is 1.3 µg/g. For our study, in order to detect a 3.5 fold change in fecal calprotectin with 90% power and alpha level of 0.05, we require a minimum of 25 subjects per group. Sample size is based on two-sample t-tests with log-transformed values.

With rolling recruiting and screening, we expect enroll 10–12 subjects/month, randomly assigning them to the intervention treatment groups in blinded fashion. The relatively short length and personalized nature of the intervention will reduce the likelihood of drop outs and allow us to recruit continuously until the recruitment goals are met.

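### The stated block size of four is a multiple of neither six arms nor three, so blocks cannot be balanced as written and equal arms of 25 are not assured

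*Protocol article*

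**What the plan says.** The Randomization and blinding section gives one block size: "The allocation sequence constructed using a block randomization with a block size of four". It also says "No stratification was used in the randomization", and it describes how the list is used: "This module references the provided allocation table and assigns participants based on order of enrollment".

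The same section sets the number of arms. For Phase I: "For Phase I, subjects will be randomly assigned to one of the six treatment arms outlined in" Figure 1. For Phase II: "For Phase II, subjects will be randomly assigned to one of the three treatment arms outlined in" Figure 2, followed by "The randomization scheme will be the same as Phase I".

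Tables 1 and 2 (Study design) list N = 25 in each of six arms and in each of three arms, so allocation is meant to be equal. The power calculations treat 25 as a floor: "growth using a minimum of 25 subjects per group" for malaria infectivity, and "we require a minimum of 25 subjects per group" for fecal calprotectin. No unequal ratio, second block size or incomplete-block construction is described.

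**The concern.** With equal allocation, a block is balanced only if its size is a multiple of the number of arms. A block of four leaves out at least two of the six Phase I arms. In Phase II a block of four must repeat at least one of the three arms. The stated block size therefore conflicts with the arm counts in the same section and with the equal N in the tables.

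Two things are at stake. The first is arm size, because 25 is the figure behind the power statements. The planned comparisons all use FeSO4 as reference, so a shortfall in that arm would touch every one of them. The second is balance over calendar time. Phase I baseline visits began in August 2017, with data collection expected to end in June 2019. The article itself names seasonal effects (Rationale for the placebo control in Phase I) and day-to-day assay variation (Statistical methods). With no stratification, blocking is the only device described that spreads the arms evenly over that period.

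**Working it through.** **Inputs.** Block size 4; arms 6 and 3 (Randomization and blinding). N = 25 per arm, hence 6 × 25 = 150 and 3 × 25 = 75 (Tables 1 and 2). Malaria: SD 0.202, effect 0.20. Calprotectin: log SD 1.3, 3.5-fold change. Alpha 0.05 (Power calculations and sample size). Assumed: two-sided tests, natural logs, and the 20% malaria reduction read as a difference of 0.20.

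**The plan's own figure.** Two-sample t-test power by the noncentral t, with standardized effect d = difference/SD and noncentrality d × √(n₁n₂/(n₁+n₂)):

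- Malaria: d = 0.20/0.202 = 0.990. This needs 22.4, so 23 per arm, for 90% power. Power at 25 per arm is 0.929.
- Calprotectin: d = ln 3.5/1.3 = 1.253/1.3 = 0.964. This needs 23.6, so 24 per arm. Power at 25 per arm is 0.916.

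The stated 25 per group is consistent with the 90% claimed.

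**Divisibility.**

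- 4/6 and 4/3 are not whole numbers, so balance within a block of four is impossible in either phase.
- 150/4 = 37.5 and 75/4 = 18.75, so the totals do not fill whole blocks either.
- By contrast, 150/6 = 25 blocks of six and 75/3 = 25 blocks of three each give exactly 25 per arm.

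**Possible arm sizes.** The article does not say how a block of four was filled. Two constructions were simulated, 4,000 lists each. Both are assumptions.

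| Construction | Phase | Arm sizes at 150 or 75 | Lists with 25 in every arm | Median enrolled until every arm has 25 |
|---|---|---|---|---|
| Four slots: 4 of 6 arms at random | I | smallest averages 20.9, largest 28.9 | none | 172 |
| Four slots: all 3 arms plus one random repeat | II | smallest averages 22.9, largest 27.2 | 4% | 80 |
| Four per arm (block of 24) | I | 24 to 28 | 3% | 155 |
| Four per arm (block of 12) | II | 24 to 27 | 30% | 76 |

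Under the four-per-arm construction blocks are balanced, but 150/24 = 75/12 = 6.25, so the last block is incomplete.

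**Power.**

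| Arms compared | Malaria | Calprotectin |
|---|---|---|
| 25 vs 25 | 0.929 | 0.916 |
| 24 vs 24 | 0.919 | 0.905 |
| 21 vs 25 | 0.905 | 0.889 |
| 21 vs 21 | 0.879 | 0.861 |
| Average pair, 4 of 6 at random, N = 150 | 0.925 | about 0.91 |
| Average pair, 4 of 6 at random, N = 159 | 0.939 | 0.927 |

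The average loss at 150 is about half a percentage point or less. For bacterial doubling time (1 hour, alpha 0.01), power at 25 per arm exceeds 0.999 for all three species with a stated SD.

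**The case against.** A reader might infer that the scheme cannot deliver 25 per arm. The article does not support that. The 25 is a minimum, no stop at 150 or 75 is stated, and recruitment is to continue until the goals are met. Study status reports 159 enrolled in Phase I by May 2019. A pre-built table can also hold 25 of each arm without balanced blocks. This stands, with one limit: on the 4-of-6 construction only about 6% of simulated lists have 25 in every arm by 159.

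A reader might also infer a power loss to 88% and 86%. That needs both compared arms at 21, which is the expected size of the smallest of six. The average comparison loses almost nothing. This stands too.

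Nor is balance over time wholly lost. On the 4-of-6 construction no arm repeats within a block. The outcomes are within-subject changes, Phase I has a concurrent placebo, and the malaria and bacterial analyses handle assay variation directly. Unequal arms do not bias a randomized comparison.

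Finally, the block size may be a reporting slip in a condensed article; the sentence after it is visibly garbled. That is plausible for Phase I. It does not settle Phase II, where the article directs that the same scheme be used with three arms.

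**Conclusion.** The point holds as a wrongly stated rule. A fixed block of four cannot be balanced within blocks for six or three equally allocated arms. Equal arms of 25 and even spread over calendar time are therefore not assured by the scheme as written. This part rests on arithmetic alone.

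The size of the effect rests on assumed constructions. The smallest Phase I arm averages about 21 at 150 if blocks draw four of six arms at random, and is at least 24 if four means four per arm. The average effect on power is small on either reading, so the case for correction rests on the internal contradiction and on how easily Phase II can be put right.

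**What to change.** **Phase II.** Before the first randomization, generate the allocation list in blocks that are multiples of three, for example randomly mixed blocks of 3 and 6. Replace the statement that the scheme is the same as Phase I with that block size. Blocks of three alone give exactly 25 per arm at 75. With mixed sizes, choose block counts that total 75: for example 5 blocks of three and 10 of six, 15 + 60 = 75. The article expects Phase II screening to begin in June 2019, so on its own timeline this costs one new allocation table.

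**Phase I.** Check the allocation table held by the Data Manager. If four is a reporting error, correct the stated block size. If it is what was used, describe how the blocks were built and report the actual number randomized to each arm. The cost is a short check and a wording change.

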### Hypothesis and objectives

We will robustly test our formal hypotheses yielding useful answers to the primary questions about the relative safety and efficacy of these novel forms of iron in iron-replete subjects. This study will address the major side effects of oral iron supplementation of iron-replete subjects. Specifically, we will compare the effects of two novel forms of iron and the widely used ferrous form on malaria (
*Plasmodium falciparum*) infectivity of host erythrocytes (assessed
*ex vivo*), bacterial proliferation (of selected species) in the presence of host plasma (assessed
*ex vivo*), redox stress and inflammatory stress (assessed
*in vivo*), gut irritation (assessed
*in vivo*), effects on the gut microbiome (assessed
*in vivo*). This set of indicators is referred to as the “safety profile”. Additionally, iron utilization (assessed
*in vivo*) will be compared to evaluate efficacy.

In Phase I, we will test the following research questions underpinning formal hypotheses using the design detailed below:

1. Does IHAT, a novel form of iron, produce beneficial and/or adverse effects comparable to FeSO
_4_ at equivalent iron doses?

IHAT and FeSO
_4_ administered at 60 mg Fe/day will produce comparable responses in malaria infectivity, bacterial proliferation, and iron status parameters. However, IHAT will produce less gut/systemic inflammation, and fewer effects on the microbiome.

2. Does Asprion, a novel form of iron, produce beneficial and/or adverse effects comparable to FeSO
_4_ at equivalent iron doses?

Aspiron and FeSO
_4_ administered at 60 mg Fe/day will produce comparable responses in malaria infectivity, bacterial proliferation, and iron status parameters. However, Aspiron will produce less gut/systemic inflammation, and fewer effects on the microbiome.

3. Are the adverse effects of FeSO
_4_ affected by co-administration of a multi-micronutrient powder (MNP)?

The safety profile of FeSO
_4_ for iron-replete individuals is not affected by its administration with a multiple micronutrient powder.

4. Are the beneficial and/or adverse effects of FeSO
_4 _comparable when administered daily or weekly?

The timing of FeSO
_4_ administration will not affect malaria infectivity, bacterial proliferation, and iron status parameters; however, weekly administration will produce less gut/ systemic inflammation and fewer effects on the microbiome.

In Phase II, we will test the following formal hypotheses using the design detailed below:

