***Exclusion criteria.*** Any major illness or condition that may interfere with study outcomes at the discretion of the study physician; personal history of glucose-6-phosphate dehydrogenase deficiency; type 1 or type 2 diabetes, or use of any pharmacological treatment for diabetes; endocrine disorders including unstable thyroid disease (dose adjustment of thyroid replacement in the past 6 months), adrenal disease, pheochromocytoma or parathyroid disease; recent history of inflammatory diseases; use of TNF blockade medication, methotrexate, or other immune-modulating drugs; steroid use (except for non-prescription topical and nasal steroids); change in dose regiment in past month or expected change during course of study if using hormone replacement therapy with estrogen, testosterone or growth hormone; history of myocardial infarction, stroke or total ischemic attack, coronary artery bypass graft, stenosis >50% diagnosed within the past year or acute unstable cardiovascular disease; clotting/bleeding disorders or ongoing anticoagulant use; gastrointestinal (GI) diseases, conditions or medications known to influence GI absorption; history of stomach or bowel resection (other than appendectomy), gastric bypass or other bariatric weight loss procedure; regular use (>2 times per week) of acid lowering medication; history of eating disorder anorexia, bulimia or binge-eating in the past 5 years; actively undergoing dialysis; inadequately controlled hypertension, certain psychiatric disorders; immunodeficiency condition, HIV or AIDS; cancer of any type (except for non-melanoma skin) or cancer therapy in past year; actively using cancer chemotherapeutic agents; regular use of ASA, NSAIDs or Cox-2 inhibitors; infection or febrile illness within two weeks prior to study or study blood draws; history, vaccination or treatment for malaria, or antimalarial prophylaxis in past 3 months; vaccinations (excluding malaria vaccine) <72 hours prior to all blood draws; unmanaged seizure disorders; history of splenectomy; chronic liver disease; use of fiber supplements, laxatives or stool softeners; colonoscopy procedure or prep within 2 months prior to or during study; predicted or anticipated antibiotic use within 3 months prior to or during study participation; unwilling to maintain dose regimen during study if using probiotic or prebiotic; inability to deliver stool sample within 18 hours of bowel movement; alcohol use on average >2 servings/day or >14 servings/week or self-reported binge drinking; current use of iron; unwilling to stop all dietary supplement, vitamins (except calcium or vitamin D), minerals, herbal other plant-based preparations, fish oil supplements or homeopathic remedies use at least one month prior to study; inadequate venous access or history of a bilateral mastectomy with nodal dissection; participation in other research study during the same time period; no social security number; iron saturation outside of normal range; hemoglobin <11.7 (females) <13.2 (males); serum creatinine >1.5 mg/dl; fasting blood sugar ≥126 mg/dL; SGOT >1.5 x upper range of normal; SGPT >1.5X upper range of normal mg/dL in absence of benign cause.

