***Stool samples.*** Subjects will be asked to provide a sample at baseline and post-intervention visits Subjects will receive stool sample collection kit at the enrollment visit to bring the samples to study visits. The stool sample in the collection container will be placed in a plastic bag, surrounded by frozen gel packs to keep it cool for up to 18 hours. Aliquots of homogenized stool will be created and the following parameters will be assessed: fecal immunochemical tests (FIT) (OC-Auto Micro 80 Analyzer); calprotectin (commercial ELISA, R&D Systems,
^30^); myeloperoxidase (commercial ELISA, R&D Systems); neopterin (competitive ELISA, ALPCO, Salem, NH); inflammatory cytokines (Meso Scale Discovery, MSD); alpha-1 antitrypsin (commercial ELISA, R&D Systems); short chain fatty acids (derivatized and analyzed by LC-MS
^31^); microbiome DNA sequencing (stool DNA extracted using the QIAamp DNA Stool Mini kit, Qiagen, Valencia, CA, and amplicons of the V4 region of the bacterial 16S ribosomal DNA will be generated using primers
^32^. Amplicons will be purified on Angencourt AMpure XP beads (Beckman Coulter, Brea, CA) before submission to the Tufts University Core Facility for 250 bp paired-end sequencing on an Illumina MiSeq. Marker-gene sequencing data will be processed using the Quantitative Insights Into Microbial Ecology (QIIME) package
^33^.

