### Rationale for inclusion of weekly intervention group in Phase I

This study will examine the effects on the “safety profile” of FeSO
_4_ administered daily (60 mg iron/day) compared to weekly (420 mg iron administered in one dose/week). In the treatment of iron deficiency, weekly supplementation has been recommended as it presents feasibility and economic advantages to daily supplementation. In various populations, including iron-deficient, anemic lactating women
^42^, non-anemic pregnant women
^43^, non-anemic pregnant women
^44,
45^ and iron-deficient, anemic school-aged children
^46^, it has been demonstrated that a weekly dose of FeSO
_4_ can be as effective in improving iron status parameters, but produce lower GI complaints, compared to daily supplementation. Although these studies support the hypothesis that weekly FeSO
_4_ supplementation is advantageous over daily supplementation, few studies have directly assessed adverse effects of weekly iron supplementation administration. Inclusion of a weekly FeSO
_4_ intervention group in Phase I presents great practical value to support the existing literature in pregnant and early-postpartum women that weekly supplementation of FeSO
_4_ is advantageous over daily supplementation.

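### Week-4 stool and fasting blood fall about 6–7 days after a weekly dose but about 1 day after a daily dose, which can make weekly iron look gentler on the gut

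*Protocol article*

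**What the plan says.** Table 1 of the protocol article sets 60 mg Fe daily against 420 mg Fe weekly. The rationale for the weekly arm makes clear that the 420 mg is a single dose, and Randomization and blinding says: "The weekly intervention group will receive four physically similar capsules once per week".

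Study timeline and visits fixes the order of events at baseline: "a stool sample, fasted blood sample and questionnaire assessing signs and symptoms of gastrointestinal health (Gut Irritation Questionnaire) are collected, followed by standard" breakfast, and then "Immediately following breakfast, subjects will be administered the assigned intervention agent". A second blood sample follows 2 hours later. For week 4: "After the 4-week intervention, subjects return for a post-intervention visit which follows the same procedures as the baseline visit".

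Stool must be fresh. One exclusion criterion is "inability to deliver stool sample within 18 hours of bowel movement", and the container is "surrounded by frozen gel packs to keep it cool for up to 18 hours". Table 3 shows stool at weeks 0 and 4 only, and Statistical methods analyses the 4-week change.

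The gut hypothesis for this comparison is directional: "weekly administration will produce less gut/ systemic inflammation and fewer effects on the microbiome".

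**The concern.** The two arms are sampled at very different distances from their last dose. The daily arm is seen about a day after 60 mg. The weekly arm, on the implied schedule, is seen at the end of a 6–7 day gap after 420 mg. If calprotectin, microbiota or fasting inflammatory markers respond to a dose and then settle over some days, the weekly arm is measured when most of its response has gone. The trial could then report less gut inflammation with weekly dosing although the two regimens irritate the gut equally per milligram.

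The stakes are real but bounded. Fecal calprotectin is a primary outcome, and the rationale section intends the weekly arm to support weekly dosing as advantageous. Only one of the four Phase I questions is affected. The comparisons of the novel irons with daily ferrous sulfate are not, and Phase II has no weekly arm.

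**Working it through.** **1. Lag from last dose to sample.** Weekly doses counted from the supervised day-0 dose fall on days 0, 7, 14 and 21. The day-28 dose follows the stool and fasting blood. The last weekly dose is thus 28 − 21 = 7 days before the visit. It is 6 days if home dosing starts on day 1, and the 18-hour limit on stool also allows a little under 7 days. The last daily dose is on day 27, about 1 day before.

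**2. Cumulative iron before the week-4 samples.** Daily 60 × 28 = 1680 mg; weekly 420 × 4 = 1680 mg. The arms differ in timing, not in total.

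**3. Direction.** Let f(t) be the response per 60 mg left after t days, and let it only decline. One 420 mg dose 7 days ago contributes 7·f(7). The seven daily doses of the same week contribute f(1) + … + f(7), which is at least 7·f(7). At a 7-day lag the weekly arm cannot look worse, even if the regimens are equally irritating per milligram.

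**4. Size.** The documents give no time course, so the half-life h is an assumption. With q = 0.5^(1/h), lag L and response proportional to dose:

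- daily: 60·q(1 − q^28)/(1 − q)
- weekly: 420·q^L(1 − q^28)/(1 − q^7)
- ratio: R = 7·q^(L−1)·(1 − q)/(1 − q^7)

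Example for h = 1 and L = 7: 7 × (1/64) × 0.5/(1 − 1/128) = 0.055.

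| Half-life (days) | R, lag 7 | R, lag 6 | R, lag 3 | R, lag 1 | 28-day mean response, weekly/daily |
|---|---|---|---|---|---|
| 1 | 0.06 | 0.11 | 0.88 | 3.53 | 1.035 |
| 3 | 0.45 | 0.57 | 1.13 | 1.80 | 1.087 |
| 7 | 0.73 | 0.80 | 1.08 | 1.32 | 1.129 |
| 28 | 0.93 | 0.95 | 1.02 | 1.08 | 1.180 |

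At lags of 6–7 days the visit ratio is below 1 throughout, while the mean response over the 28 days is not lower with weekly dosing. At a lag of 1 day the direction reverses.

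**5. On the plan's own calprotectin scale.** The plan states 25 per group for a 3.5-fold change, log SD 1.3, 90% power and alpha 0.05. With ln 3.5 = 1.253 and a two-sided test, the normal approximation gives 2 × (1.960 + 1.282)² × 1.3²/1.253², rounded up to 23. The t-test needs 24, and power at 25 is 0.916. The stated figure reproduces.

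Now suppose the daily arm truly shows that 3.5-fold rise and response adds on the log scale. At lag 7, timing alone produces a log difference of (1 − R) × 1.253, with standard error 1.3 × √(2/25) = 0.368:

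| Half-life (days) | Apparent daily/weekly ratio | Chance of p < 0.05, 25 per arm |
|---|---|---|
| 1 | 3.3-fold | 0.88 |
| 3 | 2.0-fold | 0.45 |
| 7 | 1.4-fold | 0.15 |
| 28 | 1.1-fold | 0.06 |

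**6. The 2-hour draws.** Table 3 places week-4 malaria infectivity at the 2-hour draw, and bacterial proliferation, plasma cytokines, redox and iron markers are drawn there as well as fasting. If the week-4 supervised dose is the assigned one, these samples follow 420 mg in one arm and 60 mg in the other. Any acute effect there leans against weekly dosing.

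**The case against.** The strongest reply is that the lag is deduced. The article states neither the weekly dosing day nor its interval to the visit, and the full protocol may. This stands as a limit on certainty, because at a short lag the direction reverses. It does not dispose of the point, which rests on what the article does state: the order of procedures, the dosing frequency and the single post-baseline stool.

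A second reply is that days without iron are part of the weekly regimen, that both arms are sampled pre-dose at the end of their own interval, and that cumulative iron is equal. This also stands. An end-of-interval comparison is a legitimate quantity; it is just not the average over the weekly cycle, and the hypothesis is worded without that limit.

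Third, gut symptoms do not rest on the week-4 visit. Questionnaires are also completed weekly by telephone, although the timing of the calls relative to the weekly dose is not given. That largely answers the point for symptoms, but stool has no such backup.

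A reader might infer more: that the whole weekly-versus-daily comparison is biased towards weekly dosing, or that at most a quarter of an acute effect could be seen. The documents support neither. The 2-hour outcomes lean the other way. The quarter comes from 0.5^(6/h), which is 0.25 at h = 3 but 0.55 at h = 7 and 0.74 at h = 14; it also ignores the sevenfold dose and accumulation in both arms.

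**Conclusion.** The point holds for the stool outcomes and fasting markers of the weekly-versus-daily comparison, as a possible bias and not a demonstrated one. On the implied schedule these samples are at trough for the weekly arm and about a day after a dose for the daily arm, and the mismatch favours the stated gut hypothesis. With a 7-day lag, the weekly/daily ratio at equal cumulative iron is 0.06 at an assumed 1-day half-life, 0.45 at 3 days, 0.73 at 7 days and 0.93 at 28 days.

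This rests on three assumptions: weekly doses run from day 0 or day 1, response is proportional to dose, and it wanes from the time of dosing. As planned, the week-4 calprotectin and microbiome results cannot by themselves show that weekly dosing is gentler over the whole weekly cycle.

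**What to change.** Leave both regimens and the sampling schedule as they are, and make three changes to recording and reporting.

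1. From the compliance calendar that subjects already bring to the week-4 visit, record the time from last dose to each week-4 sample and report it by arm.
2. State that the weekly-versus-daily comparison of calprotectin, microbiome and fasting markers describes the end of the weekly dosing interval, and does not by itself support a claim of less gut inflammation over the whole cycle.
3. Base the symptom comparison on all the weekly telephone questionnaires, with time since last dose, rather than on the week-4 visit alone.

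An added stool sample in the days after the week-4 dose is tempting but not advised. It needs extra collection and assays, and it mostly tilts the comparison the other way (ratio about 3.5 at 24 hours with a 1-day half-life). It also comes late: Study status reports 159 enrolled by May 2019 against 6 × 25 = 150 planned, with collection due to end in June 2019.

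The cost is some calendar abstraction, a few lines of text, and a narrower claim for weekly dosing.
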